## Abstract

**Introduction:**

Hearing aids (HAs) can alleviate hearing loss; however, HA rehabilitation is frequently hampered by delayed diagnosis, suboptimal fitting and lack of systematic follow-up. Although the association between hearing loss and cognitive decline has been identified, evidence from randomised controlled trials remains limited. Addressing these gaps is essential for reducing hearing loss-related experiences and evaluating whether effective HA use could reduce the risk of cognitive decline.

**Methods and analysis:**

The healthy hearing for healthy ageing study is a proof-of-concept, single-site, two-arm parallel-group 12-month randomised controlled trial with a 12-month extended follow-up. Up to two hundred participants with hearing loss and without cognitive decline referred for an initial HA rehabilitation are recruited and randomised 1:1 to either data-driven hearing rehabilitation or standard care. The primary outcome is the change in two speech perception in noise tests validated for the Finnish language: the Finnish matrix sentence test and the digits-in-noise test. The secondary outcomes are patient-reported outcomes (eg, Hearing in Real-Life Environment and Speech, Spatial and Quality questionnaires), quality of life (eg, 15D-questionnaire), cognitive (eg, Consortium to Establish a Registry for Alzheimer’s Disease test) and psychosocial measures. Exploratory outcomes include event-related responses, cortical auditory evoked potentials, structural brain imaging and vision-related measures.

**Ethics and dissemination:**

Ethical approval has been obtained from the Regional Medical Research Ethics Committee of the well-being Services County of North Savo (approval no. 697/2023). Findings from this study will be disseminated through peer-reviewed publications, conference presentations and relevant clinical and patient communities.

**Trial registration number:**

NCT06495268

STRENGTHS AND LIMITATIONS OF THIS STUDYEmbedding the trial in routine clinical practice with recruitment through clinical referrals enhances real-world relevance and reduces selection bias.The randomised controlled design, large sample size (N up to 200) and extended duration strengthen the study in a previously underexplored area.The usual-care control arm supports real-world applicability, with variability managed through systematic tracking of key rehabilitation variables.Double-masking is implemented as far as feasible: all participants receive identical hearing aids, assessors are masked and participants are not explicitly informed of group allocation.Follow-up may be limited to capture substantial cognitive decline or incident dementia, although extended follow-up is planned.

## Introduction

 Hearing loss is a major public health concern affecting 20% of the global population (6% with moderate to complete, ie, disabling hearing loss).^1^ Hearing loss is among the leading causes of years lived with disability in older adults.^1^ Due to the ageing of the population, it is estimated that over 900 million people will have significant hearing loss by the year 2050.^2^ The Lancet Commission on dementia prevention, intervention and care identifies hearing loss as one of the most relevant, potentially modifiable risk factors for cognitive decline and dementia. The Commission estimated that eliminating hearing loss in mid-life might reduce the risk of dementia by 7%.^3^ Even though a causal relation between hearing loss and cognitive decline is yet to be established, hearing rehabilitation may be an effective intervention for reducing risk factors such as social isolation, anxiety and depression, which have been linked to hearing loss as well as cognitive decline.^4^

A recently published multicentre randomised trial (The Ageing and Cognitive Health Evaluation in Elders Study) demonstrated that hearing intervention reduced cognitive decline by 48% over 3 years in older adult participants with other risk factors for dementia.^5^ The underlying mechanisms by which hearing interventions may slow down cognitive decline remain largely unknown. Therefore, to substantiate the role of hearing interventions in reducing the risk of cognitive decline, clinical studies are needed to comprehensively explore various outcome measures and identify those that are most relevant to promote healthy ageing.

Findings on the factors determining the success of hearing aid (HA) interventions vary widely, and there is no consensus on the most relevant outcome measures for evaluating these interventions.^6
7^ This lack of agreement contributes to the infrequent validation of hearing rehabilitation outcomes in clinical settings. Consequently, there is a surprising paucity of clinical data on real-world HA use and its benefits, which hinders evidence-based decision-making.^6^ Additionally, the absence of systematic follow-up may help explain the low levels of HA adoption and compliance.

Currently, the success of hearing rehabilitation is most often evaluated using patient-reported outcome measures (PROMs). Despite being low cost, PROMs are rarely implemented in hearing rehabilitation processes for older adults in clinics. While PROMs provide valuable insights into a patient’s subjective experiences and perceptions, they are insufficient and unreliable for evaluating audiological outcomes, as the results do not necessarily align with objective measurements.^8^ Older adults, in particular, have been shown to underestimate the degree of their hearing loss in PROMs.^9^ Additionally, many hearing-related PROMs have not been adequately validated, further decreasing their reliability.

Performance-based measures, such as speech intelligibility in noise (SPIN), can be particularly effective in capturing the everyday challenges posed by hearing loss. SPIN evaluates an individual’s ability to understand speech in noisy or reverberant environments and is currently the most appropriate measure of the real-world impact of hearing loss. Therefore, systematically measuring pre- and post-intervention SPIN could provide valuable data about the relevant factors for hearing rehabilitation.

Electrophysiological measurements of auditory pathways would represent another promising approach for the objective assessment of hearing loss and HA effects. Clinical studies have demonstrated that regular HA use can modify the auditory system, often referred to as acclimatisation to HA use. Acclimatisation is a process in which HA users not only become gradually accustomed to amplification but also gradually develop better hearing performance. However, the potential extent of adaptation of a given individual’s auditory system remains largely unknown.^10
11^ It is also unclear whether HAs can induce beneficial plastic changes in perceptual functions relevant to SPIN. The possible neural mechanisms triggered by HA use are still unknown, and if neural changes occur, the physiological mechanisms underlying these changes are yet to be determined.^12^

Dual sensory impairment (DSI) refers to the presence of both hearing and vision loss, with a prevalence between 10% and 20% in older adults (> 70 years).^13^ Previously, hearing and vision loss have been independently linked to a higher risk of cognitive decline; however, the impact of DSI on this risk remains inconclusive.^14^ It has been demonstrated that the concerns in DSI are considerably greater than the effects of vision or hearing loss alone, since individuals with dual sensory differences may experience greater activity limitations and participation restrictions than those with hearing or vision loss alone.^15^ Currently, there are no best-practice guidelines for the rehabilitation of individuals with DSI.

The healthy hearing for healthy ageing (HAHA) study is a randomised controlled trial (RCT) investigating whether considering hearing loss as a broader degenerative condition can improve both hearing and cognitive outcomes. This trial compares a data-driven hearing rehabilitation (DDHR) programme with standard care in older adults with mild to moderately severe hearing loss and without cognitive decline. DDHR is an evidence-based rehabilitation programme developed for this study in accordance with current best practices in hearing rehabilitation. Standard care corresponds to the current model of hearing rehabilitation in Finland, as described in more detail in the Methods section. The primary outcome measure is the improvement in SPIN following HA rehabilitation, serving as a key indicator for hearing function. In addition, this trial aims to address the broader neural and cognitive mechanisms, which is why we included secondary outcome measures assessing auditory processing and brain function, including structural MRI, as well as cortical auditory evoked potentials (CAEPs). These measures are intended to explore whether more effective hearing rehabilitation, reflected in improved real-world listening function, is associated with measurable neural or cognitive changes. While the DDHR programme evaluated in this trial is intended to optimise functional hearing outcomes through a more structured rehabilitation process, its implementation may require additional clinical time and resources that are not routinely available in everyday audiology practice. Consequently, an important secondary objective of this proof-of-concept study is also to evaluate the feasibility of the DDHR programme and identify strategies to support its implementation in routine clinical care. Eventually, the HAHA trial aims to establish a personalised, data-driven approach to hearing rehabilitation that could contribute to healthy ageing in older adults with hearing loss.

## Methods and analysis

### Study design

HAHA is a proof-of-concept, single-site, two-arm parallel group, 12-month RCT with a 12-month extended follow-up (figure 1). Eligible participants are randomly allocated 1:1 to either the DDHR programme (active group) or the standard care (control group). In this study, ‘data-driven hearing rehabilitation’ refers to a structured, clinician-led fitting approach in which established verification procedures are used to ensure accurate amplification, combined with the systematic use of objective outcome measures (eg, SPIN performance, HA usage data and PROMs) to guide rehabilitation decisions according to predefined criteria. This approach is clinician-implemented and does not involve algorithmic or artificial intelligence-based decision-making. Standard care corresponds to the routine hearing rehabilitation programme currently provided at the Kuopio University Hospital (KUH) ENT clinic. HAs will be fitted using the manufacturers’ proprietary fitting algorithms, and real-ear measurements (REM) will be performed only in complex cases, based on the clinical judgement of the audiometrician. The main difference is that routine standard care does not typically include systematic assessment of rehabilitation outcomes, which may contribute to suboptimal outcomes and reduced adherence to HA use. To ensure a balanced distribution between the groups, randomisation is performed using a computer-generated list in blocks of four and with sealed envelopes. The list and the envelopes are prepared by a biostatistician and used by a study nurse to randomise the participants. Although double-masking is not possible, outcome assessors will be masked to the group allocation. Participants will not be actively informed of their group allocation; however, complete masking may not be feasible based on differences between the HA fitting protocols. The HAHA trial is completely embedded in clinical practice, and all trial participants will receive the same HAs as in routine care. Due to its pragmatic approach, the HAHA trial will follow the standard care wait-time (3–6 months) for the primary HA fitting visit, which marks the beginning of the intervention. Analyses will follow CONSORT guidelines^16^ and will include the intention-to-treat population, that is, all randomised participants, except for those who withdraw their consent (including for use of data). The Standard Protocol Items: Recommendations for Interventional Trials checklist^17
18^ is also included in the present protocol paper (online supplemental material S1).

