### Participants

Up to 200 older adults (65–84 years of age) with mild to moderately severe sensorineural hearing loss^1^ are recruited from October 2024 onwards at the KUH among patients referred to the ENT clinic for HA rehabilitation of sensorineural hearing loss. Patients with conductive or asymmetrical hearing loss, HA contraindications, diagnosed cognitive impairment or cognitive concern under evaluation or any health condition affecting their ability to participate in the study are excluded. The eligibility criteria for the trial are presented in table 1. Patients are first screened as part of their routine hearing loss assessment appointment by an ENT specialist, and eligible patients are invited to participate in the study. A study nurse will obtain informed consent from the participants during the same appointment (online supplemental material S2). The recruitment for this study started on 1 October 2024, and the anticipated primary completion date is estimated to be 29 February 2028.

**Table 1 T1:** Eligibility criteria

Inclusion criteria	Exclusion criteria
Age 65–84 years	Conductive hearing impairment (air-bone gap>20 dB HL in two consecutive frequencies)
Mild to moderately severe sensorineural hearing loss, pure-tone average (0.5–4 kHz) between 20 and 64 dB*	Difference between the hearing levels of the ears is >15 dB HL in three consecutive frequencies
Community-dwelling, that is, living at home/not living in a care home or nursing home	HA contraindication
Proficiency in Finnish language	Cognitive status: Previously diagnosed dementia or current use of cholinesterase inhibitors and/or memantine. If there is a current ongoing diagnostic process for suspected dementia, the decision on eligibility will be made by an experienced study physician based on medical records and clinical judgement.
First-time HA user	Any health conditions severely impairing vision (no predefined visual acuity threshold), mobility, communication or ability to participate in study visits and complete study assessments, as judged by the study nurse and/or physician.

* As per the Global Burden of Disease Expert Group on hearing loss criteria.

dB HL, decibel hearing level; HA, hearing aid.

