### Data collection

Eligible participants (table 1) are undergoing baseline assessments prior to randomisation. The same outcome assessments will be repeated at 12-month and 24-month follow-up visits after the beginning of the intervention, which is defined by the date of the first HA fitting appointment. Table 2 and online supplemental material S3 summarise the time schedule of the HAHA assessments. All outcome assessments are performed by study nurses specifically trained in the HAHA study procedures, who are masked to participants’ group allocation.

**Table 2 T2:** Schedule of enrolment, interventions and assessments of the HAHA trial

	Study period						
	Pre-enrolment	Enrolment baseline assessment and allocation*	Post-allocation				Close-out
TIMEPOINT**	Screening	Baseline	Primary fitting visit (t_0_)	3 M	6 M	12 M	24 M
ENROLMENT:							
Eligibility screening†	X						
Informed consent		X					
Allocation		X					
INTERVENTIONS:							
DDHR intervention							
Standard care							
Primary HA fitting (all participants)			X				
Re-fitting DDHR				X‡	X‡	X‡	X‡
Standard care follow-up phone call				X			
Standard care possible additional visits§							
ASSESSMENTS:							
Screening and baseline variables¶	X	X					
Outcomes variables**		X				X	X
REAR measures††			X				

* Enrolment will take place after the screening assessment that is conducted as part of the standard ENT clinical and diagnostic work-up; to prevent allocation affecting the baseline assessments, the primary outcome assessments will be conducted before allocation. The intervention will start as soon as possible after allocation, based on the timeline for HA fitting as part of the standard clinical management of the patients.

† The screening assessment is conducted prior to enrolment as part of the standard ENT clinical and diagnostic work-up.

‡ As needed based on participant feedback, the DIN test results and/or clinical judgement.

§ As needed based on participant request.

¶ For the full list of assessments, see the ‘Eligibility’ and ‘General Covariates’ sections of the Supplementary material S3.

** For the full list of assessments see ‘General Covariates’; ‘Medical History’; ‘Anthropometrics’; ‘Primary Outcomes’; ‘Secondary Outcomes’; ‘Cognitive Measures’; ‘Quality of life and other psycho-social measures’; ‘Exploratory/Optional Assessments’; ‘Vision-related measures’ and ‘Blood samples’ sections of the Supplementary material 3.

†† DDHR group.

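### A fixed, published block of four at a single site, with envelopes used by a study nurse, lets up to a third of allocations be deduced in advance

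*Protocol article*

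**What the plan says.** Under Study design, the trial is single-site with two parallel arms allocated 1:1, and "randomisation is performed using a computer-generated list in blocks of four and with sealed envelopes". The next sentence reads: "The list and the envelopes are prepared by a biostatistician and used by a study nurse to randomise the participants". No other block size and no stratification factor is given.

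Other tasks also fall to study nurses:

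- **Consent** (Participants): "A study nurse will obtain informed consent from the participants during the same appointment".
- **Eligibility** (Participants, Table 1): the last exclusion concerns health conditions that would stop someone taking part, and it applies "as judged by the study nurse and/or physician".
- **Outcome assessment** (Data collection): "All outcome assessments are performed by study nurses specifically trained in the HAHA study procedures, who are masked" to allocation.

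Three safeguards are stated:

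- **Screening** (Participants): "Patients are first screened as part of their routine hearing loss assessment appointment by an ENT specialist".
- **Order of baseline and allocation** (first footnote to Table 2): the primary outcomes are measured at baseline before allocation, so that allocation cannot affect them.
- **Masking** (Study design): outcome assessors are masked and participants are not actively told their arm, although the same paragraph accepts that participants may work it out.

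**The concern.** Sealed envelopes hide the next allocation only from someone who cannot work it out from those already opened. With one site, apparently one list and a known block of four, the arms already used in the current block reveal much about the next arm and sometimes settle it.

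This matters because decisions are still open when the next arm can be guessed: whether to invite or consent the patient, whether to apply the one exclusion that rests on judgement, and how the baseline tests are run. The footnote to Table 2 protects baseline only if the coming arm is unknown, and the order of events alone does not ensure that. Under Statistics, the unaided baseline enters the primary analysis of change directly. Participant masking is admitted to be uncertain, so the trial leans heavily on concealment of allocation and on masked assessment.

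**Working it through.** **Inputs.** Block size 4, one site, 1:1 allocation (Study design); 180 participants required and up to 200 recruited (Statistics). Two assumptions are added: a single unstratified list, and an observer who knows the block size and has seen every earlier envelope in the block. The plan gives no figure for predictability. Its sample size does not depend on block size. It also reproduces: a Welch t-test with the stated means and SDs, two-sided 2.5% and 90% power needs 81 per group, and 81/0.9 = 90 per group.

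**Step 1: enumerate the block.** Six sequences are equally likely: AABB, ABAB, ABBA, BAAB, BABA, BBAA. The best guess is always the arm with more places left.

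| Position | Known with certainty | Best guess correct |
|---|---|---|
| 1 | 0 | 1/2 |
| 2 | 0 | 2/3 |
| 3 | 1/3 (after AA or BB) | 1/3 × 1 + 2/3 × 1/2 = 2/3 |
| 4 | 1 | 1 |

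**Step 2: average over the block.**

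- Certain in advance: (0 + 0 + 1/3 + 1)/4 = 1/3.
- Guessed correctly: (0.5 + 0.667 + 0.667 + 1)/4 = 0.708, against 0.50 under simple randomisation.

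**Step 3: scale to the trial.**

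- 180 participants: 180 × 1/3 = 60 certain.
- 200 participants: 200 × 1/3 ≈ 67 certain, and 200 × 0.708 ≈ 142 guessed correctly.

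These are expected counts for an observer who has seen every earlier envelope. They are lower if several nurses share the task without sharing allocations.

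**Step 4: would a larger known block be enough?** The same enumeration gives:

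| Known fixed block | Certain | Guessed correctly |
|---|---|---|
| 4 | 33.3% | 70.8% |
| 6 | 25.0% | 68.3% |
| 8 | 20.0% | 66.6% |

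A larger fixed block gains little.

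**Step 5: what undisclosed varying sizes change.** If staff know neither the sizes nor the set they are drawn from, they cannot tell where a block ends, so no allocation is certain in advance. A lean in the tally remains: every block ends in balance, so naming the arm that is behind still beats chance. If sizes 4, 6 and 8 are equally frequent (an illustration), that rule is right (4 × 0.708 + 6 × 0.683 + 8 × 0.666)/18 ≈ 0.681 of the time. The gain is mainly the loss of certainty, from one third to none. The rest depends on who sees the envelopes.

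**The case against.** The strongest reply is that sharing a role is not being the same person. The article has one study nurse using the envelopes and several study nurses, said to be masked, doing the assessments. That is compatible with a separate allocating nurse. Which nurse does what is a detail that an article may leave to the full protocol, which is not shown. This stands. A reader might infer that the nurse who randomises a participant later tests that participant unmasked, but the text does not say so. Nor is the trial open apart from its envelopes: assessors are masked, and both arms receive the same hearing aids.

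The safeguards also narrow the concern. An ENT specialist screens first, and the nurse's part in eligibility is one criterion, shared with a physician. The digits-in-noise test is answered by the participant on a touch screen, which limits a tester's influence on that outcome. The matrix sentence test has spoken answers and is not protected in that way.

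Finally, the figures measure how well allocation can be guessed. They do not measure bias, and no effect on either primary outcome can be derived from them. This also stands.

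None of this answers the point about the block. A fixed block size is stated as the method and is now public, and testing baseline first does not help against an arm that can be deduced.

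**Conclusion.** The point holds as a weakness in allocation concealment that is cheap to reduce. With one list in known blocks of four, a person who has seen all earlier envelopes in the block would know at most about one third of allocations beforehand (60 of 180, 67 of 200) and guess 70.8% correctly. Enrolment and baseline testing are therefore not fully protected by placing baseline before allocation.

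The counts rest on a single unstratified list and full sight of earlier allocations. They are a ceiling and do not describe what has happened at the site. No breach of assessor masking is shown, and no bias in the results is shown.

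A reader might also infer that allocating months before the fitting visit is a fault in itself. The article explains the 3–6 month wait by routine care, and no specific bias from that interval has been identified.

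**What to change.** For the unused part of the list, have the biostatistician generate allocations in randomly varying block sizes. Neither the sizes nor the set they come from should be disclosed to site staff or published while recruitment continues.

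Keep the current timing of randomisation. Moving it to the booking of the fitting visit would change who enters the intention-to-treat population of all randomised participants, and would make early and late recruits differ.

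The cost is a short amendment, a new list and slightly looser balance. The largest possible imbalance within a block is half its size, so 2 for a block of four and 4 if blocks of eight are included. Participants already randomised are unaffected, and the sample size does not change.

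As a secondary clarification, state that the nurse who opens a participant's envelope does not take consent from, judge the eligibility of, or assess that participant. This protects best if the envelope task stays with one person, because foreknowledge comes from earlier envelopes. If the full protocol already separates these tasks, one sentence saying so is enough.
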